## Abstract

**Background:**

Atrial fibrillation is a progressive arrhythmia, the exact mechanism underlying the progressive nature of recurrent AF episodes is still unknown. Recently, it was found that key players of the protein quality control system of the cardiomyocyte, i.e. Heat Shock Proteins, protect against atrial fibrillation progression by attenuating atrial electrical and structural remodeling (electropathology). HALT & REVERSE aims to investigate the correlation between electropathology, as defined by endo- or epicardial mapping, Heat Shock Protein levels and development or recurrence of atrial fibrillation following pulmonary vein isolation, or electrical cardioversion or cardiothoracic surgery.

**Study design:**

This study is a prospective observational study. Three separate study groups are defined: (1) cardiothoracic surgery, (2) pulmonary vein isolation and (3) electrical cardioversion. An intra-operative high-resolution epicardial (group 1) or endocardial (group 2) mapping procedure of the atria is performed to study atrial electropathology. Blood samples for Heat Shock Protein determination are obtained at baseline and during the follow-up period at 3 months (group 2), 6 months (groups 1 and 2) and 1 year (group 1 and 2). Tissue samples of the right and left atrial appendages in patients in group 1 are analysed for Heat Shock Protein levels and for tissue characteristics. Early post procedural atrial fibrillation is detected by continuous rhythm monitoring, whereas late post procedural atrial fibrillation is documented by either electrocardiogram or 24-h Holter registration.

**Conclusion:**

HALT & REVERSE aims to identify the correlation between Heat Shock Protein levels and degree of electropathology. The study outcome will contribute to novel diagnostic tools for the early recognition of clinical atrial fibrillation.

Trial Registrations: Rotterdam Medical Ethical Committee MEC-2014-393, Dutch Trial Registration NTR4658

## Background

Atrial fibrillation (AF) initially presents with short, self-terminating episodes and progresses into long-lasting episodes which are unlikely to convert spontaneously to sinus rhythm [1]. The exact mechanism underlying this progression is unknown. At present, there are no diagnostic tests or biomarkers available predicting recurrences of progressive AF episodes. In daily clinical practice, we can for example, not predict which patients develop AF following cardiac surgery or AF recurrences after pulmonary vein isolation (PVI) or electrical cardioversion (ECV).

AF persistence induces atrial remodeling on an electrical, structural and contractile level, also referred to as electropathology [2]. Electrical changes such as shortening of AF cycle length and contractile dysfunction occur within days after AF onset [3, 4]. After weeks of AF persistence, structural alterations become manifest in the extracellular matrix and in cardiomyocytes [1, 5–7]. Electrical and contractile abnormalities are completely reversible within weeks or days after restoration of sinus rhythm [3, 7–10], whereas recovery from structural remodeling is slow and takes up to months [11]. This finding indicates that structural remodeling underlies AF progression and recurrences. Therefore, research is directed at identifying key pathways involved in structural remodeling.

Recently it was demonstrated that derailment of cardiomyocyte proteostasis, underlies AF progression and recurrences [12–15]. Cells, including cardiomyocytes, depend for proper functioning on the maintenance of proteostasis: the balance in protein synthesis, folding, assembling, trafficking, and clearance [16, 17] (Fig. 1). Chaperones, mainly consisting of Heat Shock Proteins (HSPs), assist in the maintenance of proteostasis [17–19]. Upon acute stress e.g. in paroxysmal AF, HSPs are upregulated [20]. The progressive nature of AF lies in the gradual, often age-related, exhaustion of the HSP levels and subsequent derailment of proteostasis, resulting in structural remodeling and contractile dysfunction of cardiomyocytes (Fig. 2). Therefore, compounds that boost HSP expression, such as geranylgeranylacetone (GGA) and GGA derivatives [21, 22], are of clinical interest. Indeed, HSPs boosting, via Heat Shock Factor-1 activation, protected against derailment of proteostasis and AF progression and recurrences in several experimental AF models, including tachypaced cardiomyocytes [23], *Drosophilas* [15] and canine models [24].

**Fig. 1 Fig1:**
[figure not shown]
Proteostasis is the balance between protein expression, folding, function and clearance in the cell. When proteins are generated at the ribosomes after translation, chaperones, such as heat shock proteins, guide proper protein folding, and when not folded correctly, they guide remodeling of the protein. Furthermore, these chaperones have a role in limiting protein aggregation and they have a role in protein degradation

**Fig. 2 Fig2:**
[figure not shown]
Concept of the HALT & REVERSE project. In the normal heart Protein Quality Control (PQC) and the Heat Shock Response (HSR, *upper panel*: *green area*) maintain proteostasis in times of stress. However, with the duration of AF and with increasing age, the heat shock protein (HSP) levels get exhausted. This leads to a derailment of proteostasis (*upper panel*: *red area*), resulting in structural remodeling and contractile dysfunction of cardiomyocytes, because of, amongst others, degradation of sarcomers (myolysis, *left* and *right lower panel*). AF progresses in time (*upper panel*: *solid line*), which is rooted in the underlying electropathology. By pharmacological boosting of HSPs, we aim to HALT or even REVERSE atrial electropathology and consequently AF progression (*upper panel*: *dashed line*)

The HALT & REVERSE (*H**sf1**A**ctivators**L**ower**C**ardiomyocyt damage:**T**owards a novel approach to**REVERSE**atrial fibrillation*, MEC 2014-393, NTR 4658) project focusses on the correlation between HSPs and progression of electropathology [2]. Hereto, the HSP levels in blood and atrial tissue samples are determined and related to electrophysiological characteristics of the atria obtained from epicardial mapping during cardiothoracic surgery and endovascular mapping during PVI. The findings will elucidate whether HSP levels and electrophysiological characteristics represent a novel diagnostic tool (a so-called “bio-electrical fingerprint”) to predict the clinical outcome for AF patients and/or cardiac surgery.

## Study design

HALT & REVERSE is a prospective observational study, with a planned duration of 48 months. This study is carried out according to the principals of the Declaration of Helsinki Version and in accordance with the Medical Research involving Human Subjects Act. The study is approved by the Rotterdam local medical ethical committee (MEC 2014-393).

### Study objectives

The primary study objectives are to test the correlation between atrial electropathology as visualised by high-resolution epicardial mapping or endovascular mapping, HSP levels, atrial tissue characteristics and clinical characteristics in patients undergoing either open chest cardiac surgery, PVI or ECV. Secondly, the correlation between HSP levels and development or recurrence of AF in patients undergoing cardiothoracic surgery, PVI or ECV is tested.

### Study population

For the HALT & REVERSE project, three separate study groups are defined, consisting of patients scheduled for (1) cardiothoracic surgery, (2) PVI and (3) ECV for symptomatic AF. Each group contains 100 consecutive patients. Patients are recruited at the Department of Cardiothoracic Surgery or at the Department of Cardiology at the Erasmus Medical Center, Rotterdam, The Netherlands. Prior to enrolling in the study, each patient is provided an oral and a written explanation of the study procedure. Written informed consent is obtained from all patients.

Blood samples for baseline HSP level determination taken from all patients prior to the scheduled intervention (surgery, PVI or ECV) (Fig. 3). Patient characteristics (e.g. age, medical history, cardiovascular risk factors) are obtained from the patient’s file.

**Fig. 3 Fig3:**
[figure not shown]
Timecourse of the HALT & REVERSE project. A baseline blood sample (*red bar*) is obtained from all patients 1 day prior to the procedure. In the pulmonary vein isolation—and cardiac surgery group, the study procedure (*black bar* epicardial or endocardial mapping procedure) is performed during the elective therapeutic intervention (*yellow bar*) and post-procedural continuous rhythm monitoring afterwards (*green bars*). The *blue bars* indicate long term follow-up (>3 months) including a visit to the outpatient clinic with electrocardiography, blood samples and 24-h Holter recordings when indicated

### Inclusion criteria

In order to be eligible to participate in this study, all subjects must be >18 years old. In the cardiothoracic surgery group, only patients scheduled for elective cardiothoracic surgery for structural heart disease with or without a history of AF are included.

The PVI group will enrol patients with paroxysmal or (long-standing) persistent AF. The ECV group will consist of patients with symptomatic, AF presenting for electrical cardioversion.

### Exclusion criteria

A potential subject who meets any of the following criteria in all three study groups are excluded from participation in this study: paced atrial rhythm, haemodynamic instability, presence of cardiac assist devices, usage of inotropic agents prior to intervention or patients undergoing emergency or redo cardiac surgery.

### Sample size calculation

Approximately 25 % of patients undergoing cardiothoracic surgery develop early postoperative AF [25]. Estimated AF recurrence rate 1 year after PVI is 45 % as has been shown in previous studies [26–28], whereas the arrhythmia tends to recur within 1 year in 25–40 % [29–31] after ECV.

For none of our study groups, data testing the correlation between HSP and AF development or recurrence (in humans) is available. Therefore, a reliable parameter for sample size calculation is not available. Based upon the data mentioned above, we expect a pilot study with 100 patients in each group to be suitable for further determination of the exact number of patients needed to generate a power of 0.95 with a significance of 0.05.

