### Tissue analysis

All obtained blood samples and atrial tissue samples are stored at −80 °C until analysis. All samples are tested for HSP biomarkers, including HSP70 and HSP27. Biomarker levels are determined by commercially available ELISA’s and Western blot analysis.

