### Study endpoints

For all groups, endpoint of the study is reached when AF develops after cardiac surgery or recurs after ECV or PVI. The correlation between several biomarkers (HSP70, HSP27) and development or recurrences of AF is determined, but also the correlation between degree of electropathology and development or recurrences of AF. The relationship between atrial electrophysiological variables, as visualised by epicardial mapping, and structural tissue characteristics are tested. The findings will indicate whether HSP levels and/or the degree of electropathology represent a novel diagnostic tool to predict the clinical outcome of AF progression and/or recurrences.

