### Statistical analysis

The association between biomarker levels and development or recurrence of atrial fibrillation is calculated using multivariate logistic regression (for short term outcome) and cox regression models (for long-term outcome). Furthermore, Kaplan–Meier life tables are created for the three groups (cardiac surgery, PVI and ECV) and Log rank tests are used to compare the different groups.

ANOVA is utilized to compare various electrophysiological continuous parameters, for categorical parameters the Chi-square test will be used. Repeated HSP measurements are conducted by Joint modeling and mixed modeling analysis. Multiple biomarkers levels are corrected by ANOVA with Bonferoni adjustments.

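### Holm's step-down procedure should replace Bonferroni for the HSP markers: same family-wise error, never fewer rejections, and more power when both HSP70 and HSP27 relate to AF

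*Protocol article*

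**What the plan says.** Four places in the protocol article bear on this.

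- *Study endpoints* names two markers to be related to the clinical outcome: "The correlation between several biomarkers (HSP70, HSP27) and development or recurrences of AF is determined".
- *Tissue analysis* leaves the list open: "All samples are tested for HSP biomarkers, including HSP70 and HSP27". Two is therefore a minimum.
- *Statistical analysis* assigns the association between markers and AF to logistic regression (short term) and Cox regression (long term). A later paragraph, on ANOVA, chi-square tests and repeated HSP measurements, ends with the multiplicity rule: "Multiple biomarkers levels are corrected by ANOVA with Bonferoni adjustments".
- *Sample size calculation* reports that "a reliable parameter for sample size calculation is not available". It treats 100 patients per group as a pilot that should be "suitable for further determination of the exact number of patients needed to generate a power of 0.95 with a significance of 0.05". It does not mention the number of markers, and it does not say whether the 0.05 applies to each marker or to the set.

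**The concern.** Bonferroni judges every marker at 0.05 divided by the number of markers, even after one marker has already cleared that bar. Holm relaxes the threshold for the remaining markers once the strongest has been declared, at no cost in family-wise error. The study asks whether HSP levels can serve as a diagnostic tool, so a missed second informative marker is a real loss. It can be reduced without new data.

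A second, smaller matter is the power target. It is written as a single pair, "a power of 0.95 with a significance of 0.05", while the analysis section spreads error over several markers. Two people following the text could size the later study at different significance levels.

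**Working it through.** **No plan figure to reproduce.** The article computes no sample size for the 0.95 target and gives no HSP effect size, so the check works on the scale of the test statistic.

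**Inputs**

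- Significance 0.05 and power 0.95: *Sample size calculation*. Two-sided testing is assumed; the article does not state it.
- Number of markers m = 2: the two named in *Study endpoints*. This is an assumption, because the list is open.
- Correlation of the two test statistics: assumed 0, 0.3 and 0.6.
- Strength of effect: assumed. Noncentrality 1.960 + 1.645 = 3.605 gives 0.95 power at an unadjusted 0.05. A weaker value, 2.8, is also used.

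**Decision rules for two markers**

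- Bonferroni: declare a marker if |Z| > 2.241 (p ≤ 0.025).
- Holm: the larger |Z| must exceed 2.241. If it does, the other marker is declared if its |Z| > 1.960 (p ≤ 0.05).

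Everything Bonferroni declares, Holm declares too. Family-wise error stays at 0.05 or below. If both nulls are true, a false declaration needs the smaller p ≤ 0.025, which has probability at most 2 × 0.025 = 0.05. If one null is true, that marker is falsely declared only if its own p ≤ 0.05. Neither step uses the correlation.

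**Chance of declaring both**

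- Bonferroni: P(|Z1| > 2.241 and |Z2| > 2.241).
- Holm: P(|Z1| > 2.241 and |Z2| > 1.960) + P(|Z1| > 1.960 and |Z2| > 2.241) − P(both > 2.241).

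At correlation 0 and noncentrality 3.605, single-marker power is Φ(3.605 − 2.241) = 0.9136 at the strict threshold and 0.950 at the relaxed one. Bonferroni gives 0.9136² = 0.835. Holm gives 2 × 0.9136 × 0.950 − 0.835 = 0.901.

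At noncentrality 2.8 the two powers are Φ(0.559) = 0.712 and Φ(0.840) = 0.800. Bonferroni gives 0.507 and Holm 0.632.

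For the other correlations the same expressions were evaluated with the bivariate normal distribution:

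| Noncentrality | Correlation | Both declared, Bonferroni | Both declared, Holm | Per marker, Bonferroni | Per marker, Holm |
|---|---|---|---|---|---|
| 3.605 | 0 | 0.835 | 0.901 | 0.914 | 0.947 |
| 3.605 | 0.3 | 0.844 | 0.905 | 0.914 | 0.944 |
| 3.605 | 0.6 | 0.859 | 0.912 | 0.914 | 0.940 |
| 2.8 | 0 | 0.507 | 0.632 | 0.712 | 0.774 |
| 2.8 | 0.3 | 0.544 | 0.657 | 0.712 | 0.768 |
| 2.8 | 0.6 | 0.587 | 0.687 | 0.712 | 0.762 |

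The chance of declaring at least one marker is identical under the two rules, because the first step is the same. If only one marker carries an effect, its power moves from 0.914 to 0.915 at noncentrality 3.605 and from 0.712 to at most 0.714 at 2.8.

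**Secondary check: the power target.** A number sized for 0.95 at an unadjusted two-sided 0.05, then tested at 0.05/m, has per-marker power Φ(3.605 − z), where z is the two-sided critical value at 0.05/m. Restoring 0.95 multiplies the number by ((z + 1.645)/3.605)².

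| m | Level per marker | Power | Size ratio |
|---|---|---|---|
| 2 | 0.025 | 0.914 | 1.16 |
| 3 | 0.0167 | 0.887 | 1.26 |
| 4 | 0.0125 | 0.866 | 1.32 |

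With one-sided testing and m = 2 the figures are 0.908 and 1.20. None of these depends on the effect size. If the 0.05 is instead the family-wise level, the later number would be sized at 0.05/m from the start and 0.95 is kept.

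**The case against.** **The stronger reading.** A reader might infer that the power target and the Bonferroni sentence contradict each other, so that the planned sample size delivers 0.91 instead of 0.95. The article does not support this, for four reasons.

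- No number has been computed, and the 100 per group is called a pilot with no power claimed for it.
- The 0.05 is not said to be per marker. Bonferroni preserves an overall 0.05, so the two sections are compatible if that is what is meant.
- The Bonferroni sentence is tied to ANOVA. The regressions of AF on HSP levels are described separately and no correction is named there, so extending it to them is an inference.
- Nothing says that the later study will inherit this study's multiplicity rule.

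All four stand, and they reduce the sample-size matter to a request for clarity.

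**Against Holm.** Bonferroni is valid and correctly applied to a family of markers, so preferring Holm may look like taste. It is true that Bonferroni is not an error. But Holm is at least as powerful in every case with the same error guarantee, so the choice is not neutral. The real counterweight is that simultaneous confidence intervals matching Holm are less simple than Bonferroni's. The gain also depends on both markers carrying an effect.

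**Materiality.** A sample size derived from a pilot of this size will be uncertain by far more than 16%. That is fair, and it is a further reason to keep the second point secondary.

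**Conclusion.** The point holds as an inexpensive improvement to the analysis; it does not correct an error. With two markers that both carry an effect, Holm adds about 5 to 7 percentage points to the chance of declaring both when Bonferroni per-marker power is 0.91, and about 10 to 12.5 points when it is 0.71. It adds almost nothing when only one marker is informative, and nothing to the chance of finding at least one. These sizes rest on two markers, two-sided tests, normal test statistics and correlations of 0 to 0.6. The error control and the guarantee of no fewer rejections need none of the assumptions about effect or correlation.

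The note on the power target is conditional. The per-marker figure of about 0.91 arises only if the later study is sized at an unadjusted 0.05 and then tested by Bonferroni over two markers. It would be lower if more HSPs join the family.

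**What to change.** 1. In *Statistical analysis*, name Holm's procedure in place of Bonferroni wherever several HSP markers are corrected. This costs one sentence, no new data and no error control. If simultaneous confidence intervals are wanted, say how they will be formed, since they are less simple under Holm.

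2. In *Sample size calculation*, add a clause saying whether the 0.05 is per marker or shared, and by how many HSP markers. If it is shared, state that the later number will be computed at the adjusted level (0.025 for HSP70 and HSP27). Compared with unadjusted sizing, this raises the later number by about 16% for two markers.

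The two changes interact. With Holm and both markers informative, a number sized at an unadjusted 0.05 already gives per-marker power of about 0.94 to 0.95. If only one marker is informative, it still gives only about 0.91. Sizing at the adjusted level secures 0.95 in either case.

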### Intra-operative mapping procedure

High-resolution epicardial mapping of the entire atria according to a previously described mapping scheme is performed during open chest cardiac surgery [32]. A reference electrode is temporarily attached to the right atrial appendage. An indifferent electrode consists of a steel wire, placed in subcutaneous tissue. The mapping procedure will be performed using a custom made 192-site electrode array [32] with a 2 mm inter-electrode distance. Recordings are made at nine consecutive sites following a predefined mapping scheme (Fig. 4) during sinus rhythm (5 s/site), during pacing maneuvers for inducing AF (1 site, Bachman’s Bundle), and during AF (10 s/site). Pacing maneuvers will be performed with epicardial atrial fixed rate pacing at 250–300–350 beats per minute successively, using a standard temporary pacemaker device. If AF sustains until the end of the mapping procedure, sinus rhythm will be restored with 5–10 Joule synchronous electric cardioversion.

**Fig. 4 Fig4:**
[figure not shown]
Epicardial mapping scheme. *1* Left superior pulmonary vein; *2* right superior pulmonary vein; *3* left inferior pulmonary vein; *4* right inferior pulmonary vein; *5* inferior caval vein; *6* superior caval vein; *7* coronary sinus. The left and right atrium and Bachmann’s Bundle are mapped following a predefined epicardial mapping scheme along anatomical structures, by the use of an 192 polar electrode array (*green*)

After introduction cannulas of the cardiopulmonary bypass into the right atrium via the right atrial appendage (RAA) a tissue sample is obtained from the incision site in all patients. A tissue sample of the left atrial appendage (LAA) is obtained if the LAA is incised or amputated during surgery. All collected tissue samples are immediately snap-frozen in liquid nitrogen and stored at −80 °C.

After the surgical procedure, heart rhythm is continuously monitored until hospital discharge in order to detect early post-operative AF (PoAF). PoAF is defined as a complete irregular heartbeat without consistent P waves, sustaining for at least 30 s. At 6 months and 1 year after the procedure, patients visit the outpatient clinic for detection of late post-operative AF. A 12-lead electrocardiogram and a blood sample for HSP analysis are obtained. A 24-h Holter registration is performed when AF is suspected.

### Pulmonary vein isolation

An endovascular mapping procedure is performed prior to isolation of the pulmonary veins. Atrial electropathology is studied by means of programmed electrical stimulation in the right and the left atrium, including fixed rate atrial pacing, delivery of atrial extra systoles and decremental pacing maneuvers. Recordings of the right atrium are made by a decapolar catheter at the right atrial free wall and pacing is performed from the ablation catheter, which is positioned in the RAA. Mapping in the left atrium is performed by placing a Lasso catheter at the posterior wall and a decapolar catheter in the coronary sinus, while pacing from the left atrial roofline. Subsequently, the PVI is performed according to the electrophysiologist’ choice by either radiofrequency ablation or cryoballoon ablation.

According to standard care, heart rhythm is monitored continuously until discharge. Recordings are analyzed to detect early AF episodes, sustained for at least 30 s. At 3, 6 months and 1 year after the procedure, patients visit the outpatient clinic. During these visits, 12-lead ECGs and 24-h Holter registrations are performed to detect late post procedural AF recurrences and an additional blood sample is obtained for HSP level determination.

